## Abstract

**Background:**

Postoperative complications remain a major challenge in health care systems, with more than 70% of postoperative in-hospital mortality occurring in general wards. Current practice relies on intermittent spot-check monitoring of vital signs guided by track-and-trigger thresholds such as early warning scores. Evidence shows that, up to 4 hours before an adverse event, abnormal vital signs can be detected in up to 60% of patients. Continuous vital sign monitoring in general wards offers the potential to detect clinical deterioration earlier. However, prospective evaluations of continuous monitoring in general wards remain limited.

**Objective:**

This study aims to prospectively evaluate the impact of continuous vital sign monitoring in adult postoperative patients in general wards. The primary objective is to determine whether continuous vital sign monitoring reduces the time from device-defined physiological deterioration to the first objective escalation event (acknowledgment or clinical action) by the health care team. Secondary objectives are to evaluate clinical outcomes, operational impact, and both staff and patient experiences.

**Methods:**

We conducted a single-center, open-label randomized controlled trial of 200 general surgical patients, receiving continuous vital signs monitoring alongside standard care. Participants were randomized 1:1 to alerting or nonalerting groups, either real-time data and alerts visible or blinded to clinicians, respectively. The primary outcome is the time from the first device-defined physiological deterioration episode to the first objective escalation event (acknowledgment or clinical action). Exploratory outcomes evaluate time to treatment initiation, rapid response team activation, escalation of care, length of stay, mortality, alarm performance, and patient and staff experience.

**Results:**

The Ward Alerting and Ambulatory Monitoring Study (WARD-AMS) trial received ethical approval in April 2024; recruitment commenced in October 2024 and was completed by December 2025 with 200 patients enrolled. Data analysis is ongoing, with results to be submitted for publication by mid-2026.

**Conclusions:**

The WARD-AMS study is among the first prospective, randomized evaluations of continuous vital sign monitoring in real-world ward settings looking at clinical outcomes and user experience. By integrating clinical outcomes, alarm analytics, and stakeholder experiences, it aims to provide a comprehensive understanding of the benefits, limitations, and implementation challenges of continuous monitoring. Findings from this study will inform strategies to optimize response to early clinical deterioration, reducing alarm fatigue and embedding new technologies into existing routine ward practice.

## Introduction

Despite significant advancements in surgical techniques and perioperative care, postoperative complications continue to present substantial clinical challenges, negatively impacting both patient health and health care systems. Findings from the European Surgical Outcomes Study revealed that 73% of patients who died in hospital were never admitted to an intensive care unit (ICU) [1], whereas another study added that general wards experienced the highest rate of adverse events, followed by operating theaters and ICUs at 48.8%, 26.1%, and 13%, respectively [2]. Additionally, it has been shown that, up to 4 hours before cardiorespiratory arrest, 59.4% of patients have at least one abnormal vital sign and there is a stepwise increase in mortality for patients with an increasing number of abnormal vital signs [3]. Current standard-of-care intermittent monitoring protocols suggest measuring vital signs every 4 to 8 hours in a general ward. There is a sharp drop in surveillance intensity from continuous monitoring intraoperatively and in ICUs to intermittent manual checks in the ward, where clinical deterioration may go undetected [4]. Despite repeated evidence highlighting the critical role of respiratory rate as a marker of clinical deterioration, inaccuracies in manual measurements persist, with no improvements in technology to support bedside nursing practice [5-7].

Continuous vital sign monitoring systems, successfully used in ICUs, offer a promising strategy to extend enhanced surveillance to general wards, addressing some of these issues. Recent innovations have led to the development of wireless, wearable continuous vital sign monitoring devices, mitigating previous barriers such as size and restrictive tethering [8]. It is known that early mobilization within the first 24 hours after surgery promotes improved lung function, reduces thromboembolic risk, and shortens hospital stay [9,10]. Wearable vital sign monitors facilitate this by allowing for continued surveillance without tethering patients to bedside monitors [11,12]. Nevertheless, early retrospective and limited prospective before-and-after analyses have reported modest clinical benefit of these technologies when applied in general wards [13]. These observations demonstrate significant barriers related to device implementation and integration into existing health care systems. A recent systematic review and meta-analysis of randomized controlled trials looking at the outcomes of patients with continuous monitoring of vital signs in general wards demonstrated nonsignificant trends for improvements in in-hospital mortality, major events or complications, or higher-level care admission, with pooled odds ratios of 0.95, 0.71, and 0.82, respectively, and a mean reduction in length of stay of 2.12 days [13]. The randomized controlled trials evaluated were constrained by the heterogeneity of monitoring technologies (devices measuring diverse combinations of vital signs and varying alert parameters) and the inconsistent definitions of major complications. In addition, by not comparing with a standardized escalation pathway (who is exposed to the alarms and data, at which thresholds, and how does staff intervene), the review overlooked the critical influence of response workflows, limiting insight into whether outcomes reflect technology performance or differences in clinical practice. Understanding of how nursing and health care staff navigate the challenges of increased data volume, alarm fatigue, and changes in workflow must be realized to successfully use these technologies to improve morbidity and mortality beyond the ICU [14,15]. Additionally, patient knowledge, attitude, and perceptions regarding digital devices have been incompletely explored, lacking validation and weakened by selection bias [16-18].

This study aims to evaluate whether continuous vital sign monitoring reduces the time from device-defined physiological deterioration (T_0_) to the first objective escalation event (T_action), defined as acknowledgment or clinical action by the health care team, compared with the standard of care (intermittent monitoring) in postoperative adult patients in general surgical wards. Secondary aims are to evaluate the effect of continuous vital sign monitoring on escalation of care, timely intervention, and corresponding clinical outcomes. By capturing and analyzing the perspectives of nurses and patients, key stakeholders in device implementation, we seek to identify practical barriers and facilitators, thereby proposing actionable solutions to facilitate effective integration of continuous vital sign monitors into routine ward practice and enhance patient outcomes without imposing a burden upon health care professionals.

## Methods

### Study Design

A prospective, interventional randomized controlled trial will be conducted using a mixed methods approach. It is an open-label, 2-arm study that aims to recruit 200 patients over a 1-year period. Patients will be randomized using an online tool (Greenlight Guru Clinical) on a 1:1 basis into an alerting and nonalerting group ( Figure S1 in Multimedia Appendix 1). This study will be conducted on 2 postsurgical wards at the West Middlesex University Hospital, London, with a capacity of 64 beds, providing orthopedic, general surgical, urological, gastroenterological, and gynecological care.

Patients are screened after the morning ward round, and those who are expected to remain in hospital for at least 1 night are approached by the research team for consent and assessment against the inclusion and exclusion criteria. Most of these patients are postoperative, although a small number are preoperative. All patients will be fitted with a continuous vital sign monitor (Portrait Mobile; GE HealthCare) from recruitment until either discharge from hospital or transfer to another unit. This CE-marked device (European Union certificate CR-03-1004-804-22) consists of 2 wearable sensors: a wrist-mounted saturation probe measuring both the oxygen saturation and pulse rate and a chest sensor measuring the respiratory rate. Both groups will have vital signs monitored as per the standard of care, intermittently acquired every 4 to 6 hours by health care staff using the National Early Warning Score 2 for identification and escalation of a deteriorating patient [19].

Only the alerting group will have their continuous vital signs transmitted to a visible central viewer dashboard located at the nursing station and have audible alarms enabled on both the bedside hub monitor and the central viewer. All ward health care staff have access to real-time patient data and alarms; however, the nurse in charge is responsible for recognizing alarms, logging them, and informing the bedside nurse to respond appropriately. The intervention in this trial is the activation of real-time alerting through the continuous vital sign monitor, and alarms are managed entirely by the usual ward clinical team. They follow standard hospital escalation protocols, escalating deteriorating patients to the ward physician during daytime hours, the on-call physician out of hours, or the critical care outreach team. The critical care outreach team (also known as the rapid response team [RRT]) is an existing hospital team of specialized nurses who respond to acutely unwell patients requiring urgent assessment or intervention outside of the ICU. In the nonalerting group, health care staff are blinded to the continuous monitoring data.

To address alarm fatigue, several considerations have been taken. The alerting thresholds and announcement delays were derived from the Continuous Vital Sign Monitoring in Surgical Wards (COSMOS) pilot study, which conducted its initial phase by analyzing alarm data (pulse rate of <45 beats per minute [bpm] or >130 bpm sustained for ≥30 seconds, respiratory rate of <4 breaths per minute sustained for ≥30 seconds or >30 breaths per minute sustained for ≥120 seconds, apnea sustained for ≥30 seconds, and peripheral oxygen saturation of <85% sustained for ≥90 seconds or <80% without delay) [20]. These clinically validated alarm thresholds and built-in delay minimize false alerts caused by artifacts or transiently deranged vital signs. The central viewer is stationed at the nursing bay, beside the desk of the nurse in charge, who triages alarms. In addition, all ward staff received structured device training from GE HealthCare representatives focusing on correct interpretation, prioritization, and escalation of alarms.

Blinding of clinicians was not feasible as the intervention requires visible and audible alarms in real time to be recognized and acted upon by ward teams. The purpose of this study is to evaluate continuous vital sign monitoring in existing ward workflows, where staff awareness of alarms is intrinsic to the intervention itself. Several design features were incorporated to minimize performance and detection bias: all patients will receive standard-of-care monitoring, staff training was delivered similarly across both trial arms, and the primary end points were derived objectively from either device or electronic patient record (EPR) time stamps rather than relying on subjective documentation. Although some degree of behavior modification is unavoidable, these measures attempt to minimize bias.  

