#### Definition of T_0_ (Time Zero)

T_0_ is defined as the time stamp of the first device-defined deterioration episode for each patient according to the prespecified WARD-AMS deterioration criteria: pulse rate of <45 bpm or >130 bpm sustained for ≥30 seconds, respiratory rate of <4 breaths per minute sustained for ≥30 seconds or >30 breaths per minute sustained for ≥120 seconds and apnea sustained for ≥30 seconds, and peripheral oxygen saturation of <85% sustained for ≥90 seconds or <80% without delay.

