#### Definition of T_Action (Escalation Event)

T_action is defined as the earliest time stamp after T_0_ at which any of the following prespecified escalation events occurs:

Activation of an RRT call: time of official call log in the switchboard or outreach databaseUnplanned transfer to higher level of care: time of actual bed movement from the ward to the ICU, high-dependency unit (HDU), or critical care unit as recorded on the EPRNew high-acuity treatment orders (time stamp of order entry on the EPR): new intravenous (IV) fluid; new start of vasopressor or inotrope; new start of high-flow oxygen, continuous positive airway pressure, or noninvasive ventilation; and new start of broad-spectrum IV antibioticsTime stamp of alarm acknowledgment on the nursing log

For each patient with at least one eligible deterioration episode, only the first deterioration episode (first T_0_) will be included in the primary analysis. T_action is the earliest qualifying escalation event occurring after that T_0_. If at least one escalation event occurs after T_0_, the primary outcome is calculated as follows and expressed in minutes:

$$\text{Primary outcome}=T_{\text{action}}-T_{0}$$

If no escalation event occurs before censoring, the observation is right censored at the prespecified censor time (eg, end of monitoring period, discharge, death, or withdrawal from the study).

Acknowledgment of clinical deterioration can occur through several legitimate pathways in routine ward practice; therefore, relying on a single indicator may risk meaningful clinical response detection. To address this, a composite definition of T_action is chosen to ensure that the earliest objective, time-stamped event is captured. The same criteria are applied across both trial arms.

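### The claim that the primary end point comes from device or EPR time stamps does not cover alarm acknowledgment, which is taken from a nursing log and can arise only in the alerting arm

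*Protocol article*

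**What the plan says.** The Study Design section concedes that "Blinding of clinicians was not feasible as the intervention requires visible and audible alarms in real time". It then lists features meant to limit performance and detection bias, one being that "the primary end points were derived objectively from either device or electronic patient record (EPR) time stamps rather than relying on subjective documentation".

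The end point has two ends. At the start, "T_0_ is defined as the time stamp of the first device-defined deterioration episode for each patient", so T_0 comes from the device in both arms. At the finish, "T_action is the earliest qualifying escalation event occurring after that T_0". Four kinds of event qualify: an RRT call, an unplanned move to higher-level care, a new high-acuity treatment order, and the time "stamp of alarm acknowledgment on the nursing log".

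On who makes log entries and when an alarm exists, Study Design says that "the nurse in charge is responsible for recognizing alarms, logging them, and informing the bedside nurse to respond appropriately". It also says that "Only the alerting group will have their continuous vital signs transmitted to a visible central viewer dashboard", with audible alarms enabled for that group alone. For the other arm: "In the nonalerting group, health care staff are blinded to the continuous monitoring data".

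**The concern.** An open-label trial with a time-to-response outcome depends on how the response time is recorded. The article answers that worry by pointing to the source of the time stamps. For one of the four qualifying events the named source is neither the device nor the EPR. It is a nursing log, and the person responsible for logging alarms is part of the team delivering the intervention and knows the allocation.

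Because the earliest event wins, a log entry that comes before an order, call or transfer becomes the primary outcome for that patient. Acknowledging an alarm normally comes before those steps, so this is plausibly frequent in the alerting arm. It cannot happen in the nonalerting arm, where staff have no alarm to acknowledge. The estimated hazard ratio could then partly reflect how promptly and completely alarms were logged, in a component that the stated protection does not reach.

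**Working it through.** **1. Stated source against defined source**

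| Element of the primary end point | Source named in the article | Covered by the objectivity claim? |
|---|---|---|
| T_0 | Device | Yes |
| Unplanned transfer | EPR record of bed movement | Yes |
| High-acuity treatment order | EPR order entry | Yes |
| RRT call | Official log, switchboard or outreach database | Not device or EPR by name, but an official record |
| Alarm acknowledgment | Nursing log | No |

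The same list labels transfers and orders as EPR items and does not so label the nursing log. The claim in Study Design and the definition of T_action cannot both stand as written.

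**2. The plan's own figures (Sample Size section)**

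- Hazard ratio as a ratio of mean times under constant hazards: 154 / 60 = 2.57, which rounds to the stated 2.6.
- Patients with an analyzable episode: 200 × 0.15 = 30, as stated, or 100 × 0.15 = 15 per arm.

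Both reproduce.

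**3. How far the log alone could move the result (illustration)**

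Assumptions, none of them given in the article:

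- Times are exponential and independent.
- All events other than the log have a mean of 154 minutes in both arms, so there is no true effect on clinical action. The 154 is borrowed from the pilot response time.
- A log entry is possible only in the alerting arm, with mean delay m minutes, and every alarm is logged.

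Then:

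- share of alerting-arm times set by the log = 154 / (154 + m)
- mean alerting-arm time = 1 / (1/m + 1/154)
- hazard ratio = 1 + 154 / m

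| m (min) | Share set by log | Mean time (min) | Hazard ratio |
|---|---|---|---|
| 15 | 91% | 13.7 | 11.3 |
| 30 | 84% | 25.1 | 6.1 |
| 60 | 72% | 43.2 | 3.6 |
| 98.3 | 61% | 60.0 | 2.57 |
| 154 | 50% | 77.0 | 2.0 |
| 300 | 34% | 101.8 | 1.5 |

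The delay that gives the 60-minute target is m = 1 / (1/60 − 1/154) = 98.3 minutes.

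**4. Incomplete logging**

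If only a fraction q of alarms is logged, the share set by the log is q × 154 / (154 + m).

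- q = 0.75: 73% at m = 5, 54% at m = 60.
- q = 0.50: 48% at m = 5, 36% at m = 60.

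So completeness of logging matters as well as speed. With about 15 alerting-arm patients in the primary analysis, each first alarm that was handled but not logged changes the basis of the outcome for 1/15 = 6.7% of that arm.

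**The case against.** The best defence is that most of the safeguard is real. T_0 is device-derived in both arms, two of the four events carry EPR stamps, and the RRT call comes from an official log. The article offers the time stamps as one of several measures that reduce bias, and its Strengths and Limitations section admits that unblinded clinicians may introduce performance and detection bias. All of this stands. A reader might infer that the protection is absent altogether; the documents do not support that.

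A second defence is that the article does not say whether the log is on paper or electronic, or whether its time is generated at entry. That the nurse in charge's logging produces the log used for T_action is the natural reading, but it is not spelled out. A reader might infer rounding, back-dating or missing entries. Nothing in the text shows them, and they would pull in different directions: back-dating shortens alerting-arm times, missing entries lengthen them. A figure for recording error would be a guess. Nor does the article say that the sources used for control patients are automatic; they too follow staff actions, and they serve both arms.

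Third, it is tempting to conclude that the log decides most alerting-arm times. That is plausible but not established: under the assumptions above, the share falls below half if only half of alarms are logged.

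These points limit the claim but do not remove the contradiction. The full protocol may explain how the log works. But the article makes a positive statement about the primary end point that its own definition of T_action does not bear out.

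**Conclusion.** The point holds as an internal contradiction with a direct bearing on the primary outcome. The safeguard is incomplete: it does not cover acknowledgment, the one component recorded in a nursing log by staff who know the allocation and available only in the alerting arm.

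The size of the effect is not known from the article. The 98-minute result shows only that the log component could by itself reproduce the design hazard ratio of about 2.6. It rests on exponential times, complete logging and a common 154-minute mean for all other events, and it does not predict what happened in this trial. Whether the log times are accurate is open, because the article does not say how they are generated. Even an automatic stamp would settle only accuracy; it would not make acknowledgment possible in the nonalerting arm.

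**What to change.** 1. Reconcile the two sections. Limit the objectivity claim in Study Design to T_0, transfers, treatment orders and the official RRT call log. State that acknowledgment is recorded in a log kept by unblinded staff, and how its time is generated.
2. Prespecify a sensitivity analysis of time from T_0 to the first RRT call, unplanned transfer or EPR order, with the same censoring rules, and report it beside the primary result. These events can occur in both arms and are drawn from the same sources in each.
3. Report the proportion of alerting-arm first alarms that have a log entry, and the proportion of alerting-arm T_action times set by the log.
4. If the monitoring system stores acknowledgment times, use them to check the log times. The article does not mention such a record, so this must be confirmed first.

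Timing: the Results section puts data cleaning and preparation for analysis after data collection ends, while the abstract describes analysis as ongoing. The sensitivity analysis should be fixed and dated before outcomes are compared by arm. If that comparison has already been made, label it post hoc.

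Cost: no new patients. The component times are already needed for the primary composite, and the exploratory end points use several of them separately. The restricted analysis will have fewer events, from about 30 expected patients, and so wider confidence intervals. The claim of objectivity becomes weaker.

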### Sample Size

In a pilot study, approximately 15% of patients wearing the continuous vital sign monitor generated at least one physiological alarm, with an average response time of 154 minutes [21]. In this trial, we defined a clinically meaningful target as a reduction in response time from 154 minutes to 60 minutes, corresponding to an estimated hazard ratio of 2.6 for time to response between the alerting and nonalerting groups. Therefore, recruiting a minimum of 200 patients, 100 in each arm, yields at least 30 participants with analyzable alert events. This is sufficient in providing reasonable precision for estimating the primary effect size and to support analyses of secondary outcomes.

In a previous feasibility study, 969 respiratory rate alerts were generated from 276 patients, supporting the assumption that a sample size of 200 patients generates sufficient signal volume for detailed alarm analyses [21].

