### Statistical Analysis

#### Primary End Point Analysis

Among the 2 groups (blinded and unblinded), the primary comparison will be the time from device-defined deterioration to objective escalation. The primary analysis will be performed in the population of patients who experience at least one device-defined deterioration episode, restricted to only 1 episode per patient (the first). Time-to-event methods will be used, with Kaplan-Meier curves constructed for each arm to visualize the distribution of time to escalation. The primary hypothesis test will use a log-rank test comparing the survival curves between arms, and a Cox proportional hazard model will be fitted with the interventional arm as the main exposure to estimate the hazard ratio for escalation (intervention vs control) with corresponding 95% CIs. The Cox model will be adjusted for key baseline covariates (age, sex, and comorbidity burden [Charlson Comorbidity Index]).

Patients with a device-identified deterioration without an escalation event during follow-up until their censor time will be treated as right censored in all time-to-event analyses. Proportional hazard assumptions will be evaluated using standard diagnostics such as Schoenfeld residuals. If these assumptions are materially violated, alternative or supplementary summaries such as restricted mean time to escalation up to a predefined time horizon may be reported in sensitivity analyses.

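### The 30 analysable patients are an expected count, not a minimum, and limit the number of escalation events rather than count them, so the claim of reasonable precision is unsupported

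*Protocol article*

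**What the plan says.** The Sample Size section starts from a pilot in which "approximately 15% of patients wearing the continuous vital sign monitor generated at least one physiological alarm", "with an average response time of 154 minutes". The target is "a reduction in response time from 154 minutes to 60 minutes", "corresponding to an estimated hazard ratio of 2.6 for time to response". From this it concludes that "recruiting a minimum of 200 patients, 100 in each arm", "yields at least 30 participants with analyzable alert events", and adds: "This is sufficient in providing reasonable precision for estimating the primary effect size".

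The Primary End Point and Primary End Point Analysis sections restrict the analysis to patients with at least one deterioration episode and use only the first. The event is the first escalation after that episode (T_action). The test is a log-rank test, with a covariate-adjusted Cox model for the hazard ratio and its 95% confidence interval. On patients who never reach T_action, the plan says: "Patients with a device-identified deterioration without an escalation event during follow-up until their censor time will be treated as right censored".

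The Abstract (Results) and the Results section report that enrolment finished at 200 patients.

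**The concern.** Two things are wrong in the sentence that justifies the trial's size. It presents an average as a floor, and it counts patients who enter the risk set where the planned analysis depends on how many of them go on to escalate. The sufficiency sentence then rests on that count with no figure for precision behind it.

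The stake is how the primary result will be read. If the size is described as sufficient, a non-significant result may be taken as evidence of no benefit, although a true effect of the targeted size would be missed about one time in four (Schoenfeld) to one in three (simulation), even if every patient escalated. A significant result would carry an interval spanning about a factor of four. The Discussion already says the study is expected to show a reduction, so readers should know beforehand how precise the estimate can be.

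**Working it through.** **Inputs from the Sample Size section:** alarm proportion p = 0.15; N = 200, allocated 1:1; mean response times 154 and 60 minutes; hazard ratio (HR) 2.6.

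**Assumed, because the article does not state them:** two-sided 5% test (95% intervals are planned, but no alpha or sidedness is given); events split about equally between arms; censored fractions of 0%, 20% and 40%.

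**1. Reproduce the plan's figures.**
- Expected patients with T_0: 200 × 0.15 = 30.0.
- HR for exponential times: 154 / 60 = 2.57, which rounds to 2.6.

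Both reproduce. The 30 is exactly N × p, so it is the mean.

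**2. How firm is 30?** The count is Binomial(200, 0.15).
- SD = √(200 × 0.15 × 0.85) = √25.5 = 5.05, so the range is roughly 30 ± 1.96 × 5.05. The exact 2.5% and 97.5% points are 20 and 40.
- Exact P(at least 30) = 0.53, so P(fewer than 30) = 0.47.
- If the true rate is 12%, P(at least 30) = 0.12; if 18%, it is 0.89.
- For scale, a 90% chance of at least 30 at a rate of 15% would have needed about 244 patients.

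**3. From patients to events.** Every patient with a T_0 contributes at most one T_action, and those without one are censored. The number of events d is therefore no larger than the number of patients with a T_0. If that number is 30, then d ≤ 30.

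**4. Precision and power at d events.**
- SE(log HR) = 2/√d, and the 95% interval is 2.6 × exp(±1.96 × 2/√d).
- Schoenfeld power = Φ(½√d × ln 2.6 − 1.96), with ln 2.6 = 0.9555.
- At d = 30: SE = 0.365 and exp(1.96 × 0.365) = 2.05, so the interval is 2.6/2.05 to 2.6 × 2.05. Power is Φ(2.617 − 1.96) = Φ(0.657) = 0.744.

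| Censored (assumed) | Events | 95% interval around HR 2.6 | Upper/lower ratio | Schoenfeld power |
|---|---|---|---|---|
| 0% | 30 | 1.27 to 5.32 | 4.2 | 74% |
| 20% | 24 | 1.17 to 5.79 | 5.0 | 65% |
| 40% | 18 | 1.03 to 6.55 | 6.4 | 53% |

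**5. Cross-checks.**
- Freedman's form gives 68% power at 30 events.
- A log-rank simulation was run with exponential means of 60 and 154 minutes, a Binomial(100, 0.15) count of T_0 patients in each arm, and 4,000 runs. It gives 66% with no censoring. With ordinary random censoring that keeps hazards proportional, it gives 60% at about 26 events, 56% at about 22 and 46% at about 18.
- For reference only, since the plan sets no power target: 80% power at HR 2.6 would need 4 × (1.960 + 0.842)² / 0.9555² = 34.4, that is 35 events (Schoenfeld), or 40 (Freedman).

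**The case against.** **The wording is only loose.** The rate is given as approximate and 200 as a minimum, so the phrase could be read generously. This does not rescue it: enrolment closed at 200, and at the stated rate a count of 30 or more is little better than an even chance.

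**The plan makes no numerical claim that could fail.** This stands. A reader might infer that the trial misses its stated precision, or that it is shown to be inadequate. The article gives no interval width, power, alpha or required number of events, so there is no stated figure to miss. At 30 events an observed HR of 2.6 still has an interval that excludes 1, and a one-sided 5% test, which the article does not specify, would have 83% power. Whether that is reasonable is a judgement. What can be said is that nothing in the article supports the word.

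**Power might be far lower than shown here.** A reader might infer this by assuming that the same fraction of patients in both arms never escalates. The article gives no such fraction, and the assumption departs from proportional hazards and hence from the plan's own HR of 2.6. At about 21 events, simulated power ran from about 11% to about 87% depending only on how the never-escalating fraction was set in each arm. Unequal fractions are at least as plausible: a logged alarm acknowledgment counts as T_action, and staff are blinded to the monitor data in the nonalerting arm. Very low power figures are therefore not supported.

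**An article condenses the full protocol.** This is true, and the absence of a fuller power calculation is not the point. The point is the count that is stated and the conclusion drawn from it.

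**Conclusion.** The point holds in two parts and is limited in the third. First, 30 is the expected number of patients with a T_0, not a minimum: 95% range 20 to 40, with a 0.47 chance of fewer. This rests only on the plan's own 15% and 200. Second, the figure counts patients at risk. It is an upper limit on escalation events when 30 patients have a T_0, and the primary analysis depends on those events. This follows from the plan's own definitions and censoring rule. Third, the claim of reasonable precision is unsupported, not contradicted. With no censoring, 30 events give an interval of about 1.27 to 5.32 and power of about 66% to 74% at an assumed two-sided 5% level. The figures for 24 and 18 events rest on assumed censoring, since no rate is given.

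The primary end point, test, model and censoring rule are unaffected. This is an error in the justification of the trial's size, to be corrected before results are reported.

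**What to change.** In the Sample Size section:

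1. Replace the minimum of 30 with: *about 30 patients expected to have a first deterioration episode (95% range 20 to 40), which caps the number of escalation events*.
2. Replace the sufficiency sentence with the interval width by number of escalation events, for example 1.27 to 5.32 at 30 events, 1.17 to 5.79 at 24 and 1.03 to 6.55 at 18, around a hazard ratio of 2.6. If power is quoted, state the alpha and sidedness.
3. Describe the primary estimate as having limited precision.

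Because recruitment is complete, the counts of T_0 patients and T_action events, pooled over arms, could also be given before the arms are compared.

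The cost is wording only. No patients are added and no analysis changes. The one drawback is that the stated precision looks less favourable.
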